### Setting

The breadth of OnTrackNY sites provides an opportunity to examine the impacts of the COVID-19 crisis in New York State, which to date over 6% of the nation’s COVID-19 cases and 9% of deaths [14, 15]. The diversity of the 23 OnTrackNY teams enables examination of changes in settings with a high and low prevalence of COVID-19 infections and diverse regulatory and workforce environments. The OnTrackNY network includes teams that operate within variable regulations (e.g., outpatient clinics at ten community agencies, four state-operated facilities, and nine community and academic hospitals in urban, suburban, and rural areas).

### Characteristics of participants

Multi-level stakeholders, including program participants, families, providers, team leaders, agency leaders, trainers (OnTrack Central), and decision-makers at the state and local levels, will be interviewed. With the EPINET infrastructure for multi-stakeholder engagement, participants are recruited from three councils that represent OnTrackNY stakeholders, OnTrack Central, and an EPINET executive committee that was convened to provide guidance and input on the OnTrackNY LHS.

#### Participants

OnTrackNY serves young people between the ages of 16 and 30 who have experienced symptoms of non-affective psychosis for less than 2 years. Across the 23 teams, over 2200 people have received OnTrackNY treatment since the program began in 2013. Typically, young people are diagnosed with schizophrenia spectrum disorder. The average age of participants served is 21 years old, and 81% reside with family at admission to the program. The population served is diverse: 34% are non-Hispanic black, 26% Hispanic, and 25% non-Hispanic white. Furthermore, approximately 54% of participants have Medicaid, 35% have commercial insurance, and 4% are uninsured. The OnTrackNY participants’ diversity allows us to examine health equity within the context of a pandemic at multiple levels.

#### Youth and young adult leadership council (YYLC)

The YYLC (10-12 members) centers and elevates the voices and perspectives of youth and young adults who are either participants or graduates of OnTrackNY programs across New York State. Council members convene to represent and express what matters most to them in the design, delivery, and evaluation of OnTrackNY services and support youth-guided practices and principles in overall mental health systems transformation.

#### Family advisory council

The Family Advisory Council (8–10 members) offers an opportunity for family members of OnTrackNY participants to give feedback on program services and materials and share ideas on how to increase family involvement in OnTrackNY programs.

#### Provider council

The Provider Council (6–8 members) is comprised of one provider from each of the seven role-based services. The goal of the council is to provide a forum for providers to ask questions about the OnTrackNY program, share their input on the improvement of care processes in the OnTrackNY program and EPINET data infrastructure initiatives, and feedback on tools and resources for stakeholders.

#### OnTrack Central

OnTrack Central (12 trainers) is an intermediary organization that provides training and technical assistance to the OnTrackNY sites.

#### EPINET executive committee

This committee (8 members) includes state and local mental health officials, providers, payers, and youth and family advocates and provides input and advice on issues affecting OnTrackNY teams and participants.

#### Data collection

##### Aim 1 (exploration)

We will leverage the OnTrackNY stakeholder infrastructure to conduct semi-structured qualitative interviews with state/local decision-makers from New York State-Office of Mental Health, agency leadership, OnTrack Central trainers, and OnTrackNY team leaders. Using the FRAME, we will develop semi-structured interview guides for each stakeholder group to capture system-level decision-making that prompted service delivery modifications (e.g., shift to telehealth services). Interviewees will identify and briefly describe all modifications to behavioral health services during New York State’s stay at home order [16]. Interviewees will then identify the three most important modifications and their details, reasons for the modifications, and their importance. We will ask team leaders, agency leadership, and OnTrack Central trainers about their impact (e.g., positive/negative/no impact) on program staffing and functioning (e.g., location of staff, staff morale, supervision, and team coordination). The diversity of OnTrackNY sites (e.g., location, type of program, participant demographics) will allow exploration of larger contextual factors in administrative and organizational decision making across settings and how this affected team staffing and functioning.

Given the dynamic nature of adaptation, we will include ongoing, real-time tracking of modifications throughout all phases. Using the FRAME, we have a real-time tracking sheet to capture information learned from OnTrack Central role-based technical assistance calls with providers. A trained research assistant will review call notes and meet with OnTrack Central leadership weekly to track changes. These data will provide information directly from the front line of care. They will help identify new modifications and changes to previous modifications and see if they confirm, expand, or elaborate upon what we are learning. This is a novel application of the FRAME that will capture a dynamic process in real-time.

##### Aim 2 (confirmation/elaboration)

The OnTrackNY team leaders’ interviews will include questions about modifications by service component within the CSC model by phase of treatment. The FRAME will guide the development of semi-structured interview guides. Interviewees will identify modifications to the service components most relevant to their role. Then, they will identify the top 3 most important modifications and their details, reasons for the modifications, and their importance. Detailed follow-up questions will assess acceptability (e.g., comfort with telehealth sessions), feasibility (e.g., access to computer or laptop for telehealth sessions), and perceived impact (e.g., positive/negative or no impact) on care delivery.

We will conduct two focus groups with the OnTrackNY Family Advisory Council and with the Youth and Young Adult Leadership Council. Councils meet remotely to foster statewide participation. Using the FRAME, we will develop a focus group protocol to capture modifications to CSC service components. We will discuss the concept of modification with participants and ask about changes they experienced, for which service components, and why they think each change was made.

Based on our findings from the exploration phase, we will develop a set of questions about these major modifications (e.g., telehealth) and their use, acceptability, feasibility, and perceived impact. These questions will be added to existing participant self-report every 6 months and to quarterly participant- and program-level data forms. We will also develop a family survey about the major modifications and share with families via the OnTrack Family Advisory Council and teams. We will validate and elaborate on survey findings via four remote focus groups with OnTrack Central leadership, the YYLC, and the Family Advisory Council and Provider Council. Participants will be asked whether modifications are consistent with their care experience and how these may have evolved.

#### Fidelity review

Modifications/adaptations from interviews and focus groups will be reviewed by the existing 4-member OnTrackNY Fidelity Committee which meets as needed to discuss team-level fidelity reports and plans for discussing fidelity assessments with teams. The OnTrackNY Fidelity tool and FRAME criteria for rating fidelity will be used to determine if a modification is fidelity-consistent (i.e., whether the modification adheres to core CSC service components specified in the OnTrackNY Fidelity tool) or fidelity-inconsistent.

## Aim 3 (examination)

OnTrackNY’s ongoing data collection infrastructure (program and participant-level) will be used to identify how (or if) the COVID-19 crisis has impacted changes in the population being served, how or which services are being offered and utilized, and participant outcome trajectories (Table 2). Analyses will further examine how changes in each of these areas are related to one another, using the natural experiment of the COVID-19 crisis to build evidence for how participant and service characteristics within the CSC model affect participant outcomes. While we will establish trends in program and participant characteristics across the pre-COVID period (since program inception in October 2013 through March 2020), we must remain flexible in our analysis of the post March 2020 period to account for additional key dates (e.g., dates when stay at home order ends in given regions or the vaccine is distributed).

### Statistical methods

#### Aim 1

Interviews and focus groups will be audio-recorded, transcribed, and coded by two independent coders. Qualitative content will be managed using Atlas.ti software. Directed content analysis is a deductive analytical approach that derives codes from existing theories, frameworks, and constructs and is used to validate, expand, or refute theories [17, 18]. We will use FRAME dimensions to develop our initial codes and list of major modifications identified by stakeholders commenting on system-level decision making and its impact on team staffing and functioning and modifications to CSC service components. The list of major modifications from interviews and focus groups will be reviewed alongside a list of modifications generated by the ongoing, real-time tracking of modifications. In the case of divergence in type and characteristics of existing modifications or emerging modifications, the coders and study team will reconcile and revise the major modifications list. Questions to confirm major modifications and their use, acceptability, feasibility, and impact will be added to existing participant self-report, and other participant- and program-level data collection. A new survey to obtain the family perspective will be developed as part of Aim 2.

Exploring variability in modifications across the OnTrackNY network: To understand how system-level decisions impacted OnTrackNY team functioning and differences across the network, we will examine our qualitative findings using a thematic matrix analytical approach [19, 20]. This analytical process will help organize findings from each of our qualitative data sources into a matrix to compare side-by-side the different types of modification identified by stakeholders and their perceived impact. We will then generate a list of relevant system, organizational, staff, and participant-level modifications by the level of consensus (i.e., identified by more than one source) and operational salience (i.e., identified as critical). Using the same thematic matrix analytical approach, we will generate a list of relevant modifications based on OnTrackNY dimensions (location, type of program, and characteristics of participant population served) by the level of consensus (i.e., identified by more than one source) and operational salience (i.e., identified as critical).

#### Aim 2

Descriptive analyses of surveys will be conducted by stakeholder group and will explore differences in use, acceptability, feasibility, and perceived impact by different OnTrackNY dimensions (location, type of program, respondent characteristics including demographics, age, time in the program). The list of major modifications from the surveys will be reviewed alongside a list of modifications generated by the ongoing, real-time tracking of modifications. In the case of divergence in type and characteristics of existing modifications or emerging modifications, the coders and study team will reconcile and revise the list of the major modifications. Modifications that meet threshold criteria (at least 50% of all stakeholder groups identified) will be considered tier 1 modifications and used in subsequent quantitative analyses examining effects on participant-level care processes and outcomes in Aim 3 work. Modifications that do not meet these threshold criteria (tier 2 modifications) will be summarized and described based on OnTrackNY dimensions by level of operational salience.

#### Aim 3

As in prior work with OnTrackNY longitudinal data [4, 21, 22], we will utilize generalized linear mixed models which account for the natural multi-level structure of the data of repeated measures on participants (every 90 days by providers and 6-month participant self-report) nested within teams. Importantly, we will incorporate a fixed time period indicator of the pre-March 2020 period allowing for a categorical indicator for each calendar month post-March 2020 until the end of the study period (likely first quarter of 2022). Outcomes and predictors will vary depending on the question (Table 2). Still, in all cases, we will use best statistical modeling practices for estimating and testing effects (focusing on effect sizes and uncertainty using 95% confidence intervals).

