## Discussion

The rapid rise of COVID-19 created shocks to the health care system. To combat the rapid rise of infections, the New York State (NYS) stay at home order (effective March 22, 2020) required all non-essential businesses to cease in-person operations, required people to shelter in place, and move to distance technology [16]. Engagement with the OnTrackNY network revealed how these conditions have dramatically impacted CSC services. For example, many sites rapidly moved from providing 0% to nearly 100% telehealth with no time to plan, and with limited infrastructure, experience, or training. Agencies faced redeployment of staff to medical units, staff members’ childcare challenges, and illness of team members as well as agency requirements regarding the need to be on-site, which caused staff changes and disruptions. Some participants faced access barriers (limited availability of cell phones, WIFI). Moreover, telehealth may be particularly challenging in CSC treatment, with participants experiencing cognitive deficits and symptoms of psychosis [23], as well as a suicide risk. Despite these challenges, OnTrack Central has begun to learn about staff innovation and creativity that could transform these challenges to improvements and advantages. OnTrackNY teams remain committed to their mission to provide high-quality care to improve participants’ outcomes.

This crisis provides an opportunity to examine how CSC teams, facing a substantial and unexpected disruption, can respond and adapt to the changing needs of participants, families, and their own agencies, to maintain high-quality services. The health care and economic effects of the COVID-19 crisis are likely to persist for some time. Some changes in health care delivery, particularly increased use of telehealth may be permanent. It is crucial to understand the impact of these changes on service delivery and on participant outcomes [24]. This is a unique opportunity to understand how decisions to adapt service delivery are made, how they are implemented in response to the crisis, and how they impact different stakeholder groups, including policy leaders, providers, participants, and family members. This study, supported by supplementary COVID-19 funding (2021–2023), provides a unique opportunity to examining this system transformation by systematically capturing service modifications using implementation science frameworks (RE-AIM and FRAME) and dynamically examining this process as it unfolds.

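### The Aim 3 section promises pre-COVID trends, but its model codes October 2013 to March 2020 as one level with no slope, so an unmodelled trend would pass into the post-March 2020 month effects

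*Protocol article*

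**What the plan says.** The section Aim 3 (examination) commits to a pre-pandemic description over time: "we will establish trends in program and participant characteristics across the pre-COVID period", a period defined as "since program inception in October 2013 through March 2020". The same section uses the pre/post comparison to judge whether and how the crisis changed the population served, the services delivered and participant outcomes.

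Statistical methods, Aim 3, names the model class ("we will utilize generalized linear mixed models which account for the natural multi-level structure of the data") and then fixes the calendar-time coding: "we will incorporate a fixed time period indicator of the pre-March 2020 period allowing for a categorical indicator for each calendar month post-March 2020", running "until the end of the study period (likely first quarter of 2022". On other terms it says only "Outcomes and predictors will vary depending on the question (Table 2". No pre-period slope is named.

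The period labels do not quite agree. The Aim 3 section counts March 2020 as pre-COVID. Read literally, the labels in Statistical methods put March 2020 in neither period, and the title of Table 2 likewise contrasts before and after March 2020. The Discussion dates the "stay at home order (effective March 22, 2020").

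**The concern.** If the pre-period enters as one level, each post-March 2020 month is compared with the average of everything since 2013. A quantity already rising or falling before the pandemic would differ from that average in 2020–2022 even if COVID-19 had done nothing. The confidence interval would not show this, because the error is bias and not sampling noise.

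Describing pre-COVID trends separately does not adjust the contrast. The trend has to be the reference against which the later months are judged, and the article does not say that it will be. The results feed an adaptation guide meant for programmes and for state and local mental health authorities, so misattributed drift could reach practice.

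**Working it through.** **The plan's own figure.** Statistical power gives 80% power for a shift of 7%, read here as 7 percentage points, from about 25% early discharge. The period sizes behind it are not stated. With a two-sided 0.05 test of two proportions (alpha and sidedness assumed), 80% needs 652 per period for 25% vs 32%, or 540 for 25% vs 18%. With 500 vs 500 the power is 69% (rise) or 77% (fall); with 2,200 vs 500 it is 88% or 93%. The figure is plausible but cannot be confirmed. It serves below only as a yardstick.

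**Size of the bias**

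Inputs from the article:
- Pre-period: October 2013 through March 2020, 78 months, numbered 0 to 77.
- Post-period: April 2020 to about March 2022, 24 months, numbered 78 to 101, mean 89.5.

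Assumptions, because the article gives neither:
- Pre-period data are spread evenly (mean month 38.5), or enrolment grew linearly (mean month 51.33).
- The outcome drifts linearly, with no COVID-19 effect.

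Formula: spurious shift = drift per year × (post month − pre-period mean month) / 12.

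| Pre-period data | Gap to mean post month | Shift at 1 point/year: first month, average, last month | Drift giving a 7-point average shift |
|---|---|---|---|
| Even | (89.5 − 38.5)/12 = 4.25 years | 3.3, 4.25, 5.2 points | 7/4.25 = 1.6 points/year |
| Linear growth | (89.5 − 51.33)/12 = 3.18 years | 2.2, 3.2, 4.1 points | 7/3.18 = 2.2 points/year |

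The bias does not depend on clustering.

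**Enrolment.** Over 2,200 people had been served to date, with over 500 new enrollees in 2019. Even if all 2,200 had enrolled before April 2020, the pre-period average is 2,200/6.5 ≈ 338 per year. Suppose enrolment then fell to 400 per year, 20% below 500. Against the flat average this is 400/338 ≈ 1.18, an 18% rise: the sign reverses. This is for network-wide counts. If growth came mainly from new teams, per-team rates would be less affected; the article does not say.

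**False positives depend on the contrast.** Take the linear-growth gap, a 25% rate (variance 0.1875), 1,700 pre-period participants and independent observations:
- One month of 42 enrollees (about 500 per year): SE = √(0.1875/1,700 + 0.1875/42) = 6.8 points. Rejection is about 8% at 1 point/year and 16% at 2.
- Pooled post-period of 500: SE = √(0.1875/1,700 + 0.1875/500) = 2.2 points. Rejection is about 30% and 82%.
- Pooled post-period of 1,008 (24 × 42), by simulation of 1,000 runs: 45% and 95%. With a linear calendar-time term added, rejection was 5% to 7% and bias at most 0.1 point.

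These rates ignore repeated measures and clustering by team, so they are illustrative only.

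**The remedy can be estimated.** An intercept, linear time and 24 post-month indicators over 102 months give 26 columns of rank 26. The slope is then identified from the pre-period alone, and each indicator is a deviation from its projection.

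**The case against.** The strongest reply is that the article does not exclude a trend term. It promises pre-COVID trends, leaves predictors to vary by question, and is a condensed account whose fuller analysis plan is not shown. The stated coding is compatible with an added slope, so at most one term is missing. This stands: a reader might infer that every pre/post estimate in Table 2 is biased and that any secular trend will be read as a COVID-19 effect, and the text does not support that. What remains is that the article chose to fix the calendar-time coding, and the coding it fixed does not carry the trends it promises.

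Second, Table 2 lists enrolment characteristics, demographics and programme site alongside participant outcomes, so part of any case-mix drift may be adjusted for. This also stands. Such covariates would not remove drift in practice or in the outcomes themselves.

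Third, the growth described is in programme size. No drift in discharge, symptoms or functioning is documented. A drift of 2 points per year would mean a change of 2 × 6.5 = 13 points in a rate that the article gives simply as about 25% historically. This stands, so the figures for those outcomes are conditional. Enrolment is the exception, being itself a Table 2 outcome.

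Fourth, high false-positive rates come from a pooled comparison, whereas the plan has one indicator per month. This stands too: single-month tests would reject far less often. The bias in each month effect is still there.

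Finally, a reader might see the handling of March 2020 as a serious inconsistency. It concerns one month of about 102 and is a labelling matter; whether to cut at 22 March or at a month boundary is a preference.

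**Conclusion.** The point holds as a mismatch between two statements. Pre-COVID trends are promised, but the Aim 3 model as written has a single pre-period level and no term for them. An unmodelled trend would therefore enter the post-March 2020 month effects and could be taken for COVID-19 impact.

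For enrolment the growth is documented, and the distortion could be large enough to reverse a sign in network-wide counts. For other outcomes the size is an assumption: roughly 3 to 4 points of spurious average shift per point of annual drift, so that about 1.6 to 2.2 points per year would mimic the whole 7-point shift. This rests on linear drift, on even or linearly growing enrolment, and on a post-period ending in March 2022. Estimates are exposed to bias; they are not shown to be biased.

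**What to change.** In Statistical methods, Aim 3:

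1. Add a calendar-time term, linear or a spline with few degrees of freedom, with season, estimated from the pre-period. Keep the monthly indicators and report them as deviations from the projected pre-COVID trend. State that this is how the promised trends enter the model.
2. Add a sensitivity analysis restricted to the last 2–3 pre-COVID years and to teams already operating.
3. Assign March 2020 to one period and use that definition in the Aim 3 section, Statistical methods and Table 2.

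The change needs wording and code, but no new data. It costs precision. Under the linear-growth assumption the pre-period enrolment dates have a standard deviation of about 1.54 years, so the variance of the pre-period reference rises from 0.1875/1,700 to (0.1875/1,700) × (1 + 3.18²/1.54²). The SE of one month's effect (42 enrollees) then goes from 6.8 to 7.1 points, and that of the average over 1,008 post-period participants from 1.7 to 2.8 points. The results also come to rely on extrapolating the pre-trend for up to two years, which is why the restricted sensitivity analysis is needed.

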## Background

Coordinated Specialty Care (CSC) programs provide evidence-based services for young people with recent onset of a psychotic disorder [1]. New York State’s program, OnTrackNY (OTNY), is a nationally recognized model of CSC treatment [2]. The program is implemented by a multidisciplinary team with specialized training, which provides coordinated, evidence-based treatments based on the interests, needs, and preferences of each participant. The program emphasizes assertive outreach and engagement and is offered for an average of 2 years. OnTrackNY teams offer participants a range of evidence-based treatment options, including individual therapy based on cognitive behavioral therapy for psychosis (CBTp), psychiatric medications, family education and support, peer support, supported education and employment, case management and community support, and a focus on physical wellness and primary care coordination. Teams focus on helping participants attain individual goals typically related to school, work, and relationships [3]. OnTrackNY has demonstrated improvements in symptoms, functioning, hospitalization, and work/school participation [4]. Guided by the Reach, Effectiveness, Adoption, Implementation and Maintenance (RE-AIM framework), OnTrackNY program implementation has been previously described [5, 6].

OnTrack Central is an intermediary organization [7, 8] responsible for training and implementation support of OnTrackNY programs. It has created systems for multi-level stakeholder engagement, a centralized data collection protocol for quality improvement and evaluation of program fidelity, and a mechanism to support practice based-research. Initial training provided to OnTrackNY teams includes a multi-day in-person introductory training in the principles and practices of the CSC model, followed by remote consultation, and training in data collection forms, procedures, and the data collection platform. Regular, on-going training is also provided for team members, based on their specialty, through frequent individual, collaborative, role and team-based phone calls, monthly care consultation calls, webinars, and use of data and fidelity reports to highlight strengths and identify areas for improvement [3].

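### Aim 3 sets each month after March 2020 against an all-season pre-period level with no stated seasonal term, so month-specific work/school and supported-education estimates can mix the school calendar with the COVID-19 effect

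*Protocol article*

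**What the plan says.** The Aim 3 part of Statistical methods specifies generalized linear mixed models for "repeated measures on participants (every 90 days by providers and 6-month participant self-report) nested within teams". Calendar time enters through a "fixed time period indicator of the pre-March 2020 period allowing for a categorical indicator for each calendar month post-March 2020", running "until the end of the study period (likely first quarter of 2022"). The remaining terms are left open: "Outcomes and predictors will vary depending on the question (Table 2").

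The section Aim 3 (examination) adds two statements about time. For the earlier years, "we will establish trends in program and participant characteristics across the pre-COVID period (since program inception in October 2013 through March 2020"). For the later period, the analysis is to stay flexible so that it can "account for additional key dates (e.g., dates when stay at home order ends in given regions or the vaccine is distributed"). No section mentions season, month of year or the academic calendar.

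Table 2 lists work/school participation as a participant outcome and frequency of service use, including supported employment and education, as an implementation outcome. On the population, "The average age of participants served is 21 years old" (Participants), and teams help them "attain individual goals typically related to school, work, and relationships" (Background).

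**The concern.** With one indicator for the whole pre-period, the coefficient for July 2020 is July 2020 minus the average of all earlier months, winter and summer alike. A regular within-year pattern in the outcome goes into that coefficient. A pre-period slope would not remove it, because a secular trend and a yearly cycle are different things.

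The article's own description of the population makes such a pattern plausible for school-linked outcomes. The stay-at-home order took effect on March 22, 2020, so the first monthly estimates run through spring into the summer break. Monthly coefficients are useful mainly for showing when things changed and when they recovered. An ordinary summer fall and autumn return could be taken for an effect of the order, of reopening or of a service modification, and the findings feed a guide for programs and state and local authorities.

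**Working it through.** **Nearest figure in the plan.** The article gives no figure on seasonality. The closest is the Statistical power statement of 80% power for a 7% shift in early discharge from about 25%. Read as points, with a two-sided 5% test, 25% against 32% gives 81.3% power at 1000 versus 500 participants and 80.5% at 1700 versus 400, but 68.9% at 500 versus 500. The pre/post split is not stated, so the figure reproduces under plausible splits. It concerns a different quantity (see the verdict).

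**Inputs from the article.**
- Pre-period, October 2013 to March 2020: 78 months. October to March each occur 7 times and April to September each 6 times.
- June to August: 3 × 6 = 18 of 78 months, a share of 0.231.
- Post-period, April 2020 to March 2022 (if it ends with the first quarter of 2022): 24 months, each month of the year twice. June to August: 6 of 24, a share of 0.25.

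**Assumptions, not in the article.** A June to August dip of D points, no true COVID-19 effect, equal weight per pre-period month, and effects on the percentage-point scale.

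**Formula.** For a post-period window in which a share w of months is June to August, the apparent effect is -D × (w - 0.231). A single summer month has w = 1, any other month w = 0, and the pooled post-period w = 0.25. As an illustration only, a June to November window has w = 0.5.

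| D (points) | Summer month | Other month | June to November | Pooled 24 months |
|---|---|---|---|---|
| 5 | -3.8 | +1.2 | -1.3 | -0.10 |
| 10 | -7.7 | +2.3 | -2.7 | -0.19 |
| 15 | -11.5 | +3.5 | -4.0 | -0.29 |

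**Reporting windows, D = 10.** If a form averages the current and two preceding months, it carries 1/3 of the dip in June, 2/3 in July, all in August, 2/3 in September and 1/3 in October. The pre-period mean share is (6×1/3 + 6×2/3 + 6×1 + 6×2/3 + 7×1/3)/78 = 18.33/78 = 0.235. The apparent effects are then -1.0 (June, October), -4.3 (July, September) and -7.6 (August). If a form averages six months, the largest share is 3/6 (August to November). The pre-period mean share is (6×1/6 + 6×2/6 + 6×3/6 + 6×3/6 + 7×3/6 + 7×3/6 + 7×2/6 + 7×1/6)/78 = 19.5/78 = 0.25, so the largest apparent effect is -10 × (0.5 - 0.25) = -2.5.

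**A narrower dip and its false-positive rate.** If only July and August dip (12/78 = 0.154), D = 2, 5 or 10 gives -1.7, -4.2 or -8.5 points in those months and +0.3, +0.8 or +1.5 in the others. A binomial simulation used 2000 runs, a 60% baseline, 150 or 267 forms per post month, half that per pre month, and no clustering. The 95% interval for July and August wrongly excluded zero in 7–8%, 18–28% or 54–78% of runs respectively.

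**With a month-of-year term.** When the term is estimated from the pre-period, the expected bias is 0 in every month, and the simulated false-positive rate is about 5% throughout.

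**The case against.** The strongest reply is that the quoted sentence fixes only how the pandemic period is coded. Predictors are left open and best modeling practice is promised, so a month-of-year covariate could be added without changing a word, and a condensed article need not list its covariates. This stands in part. A reader might infer that the plan rejects seasonal adjustment, and the document does not support that. But the article does choose to state the time structure, and it mentions trends without mentioning season. Neither the open predictors nor the general promise supplies the term.

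Three further objections stand and limit the point:
- **Size.** No amplitude is given, and the article does not define whether a student on summer break counts as not participating. With a 2-point July–August dip the bias is small.
- **Reporting windows.** Reports every 90 days or 6 months weaken and delay the pattern. They do not abolish it: under 90-day averaging of a June–August dip, an August form keeps nearly all of it.
- **Scope.** Table 2 is headed as a pre/post comparison, and over 24 post months the bias almost cancels. The key-date passage asks for flexibility and defines no window, so seasonal mismatch arises there only if part-year windows are used. Seasonality is less evident for enrolment or general service use than for school-linked outcomes.

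**Conclusion.** The concern holds for month-specific and part-year contrasts on work/school participation and supported-education use. For a June–August dip of 5 to 15 points, the apparent effect in a summer month with no true change is about -3.8 to -11.5 points before any blurring by the reporting window. The direction follows from the stated coding. The size rests on the assumed dip, on equal weighting of pre-period months and on a seasonal pattern that is stable from year to year.

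Two stronger readings are tempting, and the document does not support them:
- **That the pre/post work/school conclusions in general are biased.** The pooled 24-month contrast moves by at most 0.29 points in the range above. The comparison described under Statistical power, steady work or education over a whole year, spans every season in both periods. Comparisons between teams within the same later month are also largely protected by the month indicators.
- **That the bias exceeds what the study is powered to detect.** The 7-point shift refers to disengagement before one year, and the similar power claimed for work/school refers to the whole-year measure. Neither is a benchmark for a single-month bias.

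Nor can it be said that a false summer fall will appear, only that the stated coding could not separate one from a pandemic effect.

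**What to change.** Where month-specific or short-window estimates are reported for work/school participation and supported-education use, state that the Aim 3 model also includes month-of-year fixed effects estimated from the October 2013 to March 2020 data. Each later month is then compared with the same calendar month in earlier years. Apply the same terms to any window set at a key date. Extend them to other outcomes if the pre-period data show a seasonal pattern. Quarter-of-year terms can serve for sparse outcomes, though they remove a summer dip less completely when it straddles two quarters.

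The terms are estimable, since each month of the year occurs 6 or 7 times in the pre-period. The cost is a change of analysis wording, up to 11 parameters in a model drawing on over 2200 participants, and slightly wider intervals. No new data are needed.
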